## Abstract

**Background:**

Early developmental interventions to prevent the high rate of neurodevelopmental problems in very preterm children, including cognitive, motor and behavioral impairments, are urgently needed. These interventions should be multi-faceted and include modules for caregivers given their high rates of mental health problems.

**Methods/Design:**

We have designed a randomized controlled trial to assess the effectiveness of a preventative care program delivered at home over the first 12 months of life for infants born very preterm (<30 weeks of gestational age) and their families, compared with standard medical follow-up. The aim of the program, delivered over nine sessions by a team comprising a physiotherapist and psychologist, is to improve infant development (cognitive, motor and language), behavioral regulation, caregiver-child interactions and caregiver mental health at 24 months' corrected age. The infants will be stratified by severity of brain white matter injury (assessed by magnetic resonance imaging) at term equivalent age, and then randomized. At 12 months' corrected age interim outcome measures will include motor development assessed using the Alberta Infant Motor Scale and the Neurological Sensory Motor Developmental Assessment. Caregivers will also complete a questionnaire at this time to obtain information on behavior, parenting, caregiver mental health, and social support. The primary outcomes are at 24 months' corrected age and include cognitive, motor and language development assessed with the Bayley Scales of Infant and Toddler Development (Bayley-III). Secondary outcomes at 24 months include caregiver-child interaction measured using an observational task, and infant behavior, parenting, caregiver mental health and social support measured via standardized parental questionnaires.

**Discussion:**

This paper presents the background, study design and protocol for a randomized controlled trial in very preterm infants utilizing a preventative care program in the first year after discharge home designed to improve cognitive, motor and behavioral outcomes of very preterm children and caregiver mental health at two-years' corrected age.

**Clinical Trial Registration Number:**

ACTRN12605000492651

## Background

With increasing numbers of very low birthweight (VLBW; <1500 g) or very preterm (<30 weeks' gestational age) infants surviving, there is a growing recognition that substantial numbers of these infants will develop motor, cognitive and behavioral problems. These disabilities have life long consequences and will soon translate into increased numbers of adults with disabilities[1]. The educational and social implications are substantial. The prevention of learning disabilities, behavior and motor problems is an important goal for modern perinatal care for preterm children and their families[2].

There are many potential factors contributing to the risk of disability in the preterm infant, including severity of illness, suboptimal nutrition, therapeutic exposures, environmental and social factors. Whilst there are many randomized controlled trials investigating medical interventions that target some of these areas, there is a paucity of sufficiently powered randomized trials involving multi-dimensional interventions focusing on environmental, behavioral, and early developmental factors [3].

This study, called VIBeS (Victorian Infant Brain Study) Plus, follows on from the earlier VIBeS study that monitored the natural history of brain development by evaluating alterations in brain structure in the early weeks after birth with advanced neuro-imaging modalities, and compared brain development, motor and behavioral outcomes at 2 years[4,5]. The current VIBeS Plus study involves a randomized controlled trial of a preventative care program with the aim to improve the infant's cognitive and motor development, behavioral regulation, as well as the primary caregiver-child interactions and primary caregiver mental health at 24 months' corrected age.

The VIBeS Plus program is partly based on a study by Dolby et al[6], with the content of this intervention package updated to incorporate several related recent theoretical frameworks of development, including dynamic systems theory[7] and family-centered care[8]. The program by Dolby et al[6] involved two teams, each of a psychologist working collaboratively with a physiotherapist to develop a strong link between behavioral regulation and motor competence. The study by Dolby et al was a quasi-randomized trial with three groups with 81 subjects entered (27 in each group) with 69 subjects completing the study in the preterm intervention group (n = 24), a preterm control group (n = 22) and a term control group (n = 23).

The program by Dolby et al[6] consisted of six sessions, with the family first seen in hospital at 36 weeks' postmenstrual age. The following sessions occurred at home: at term, 1, 4, 6 and 9 months' corrected age. Assessments and interventions were targeted to occur at the beginning of a new developmental phase, where there is often a period of disorganization prior to change[9]. At 12 months, infants in both groups were assessed by a psychologist who was masked to the infant's status (preterm vs term, and intervention vs control) using the Bayley Scales of Infant Development (BSID)[10]. The authors reported that there were significant effects in favour of the intervention group for both cognitive and motor outcomes[11].

The program by Dolby et al[6] was designed specifically for parents when their infants were at home, and was based upon the framework of the synactive model of self regulation and developmental care described by Als[12,13] and attachment theory described by Sroufe[14]. Each model described in the study of Dolby et al[6] is outlined briefly below.

### Self-regulation model

Preterm infants have been reported in many studies to have alterations in behavioral regulation compared with infants born at term[15]. These alterations in behavioral regulation may lead to a preterm infant being more irritable, taking longer to settle into a routine, and being less playful[16,17]. Als[12] proposed a synactive model of neonatal behavioral organization to help explain these alterations in neurobehavior and a framework for intervention. The underlying assumptions of the model are that five systems, including motor, state organization, autonomic, attention-interaction and self regulation systems, work continuously in an inter-relationship for the infant to function[12,18]. Any alterations within the five systems will cause functional difficulties for the infant and affect overall self regulation. Caregivers are encouraged to enhance the self regulation abilities of the individual baby by supporting any of the five systems, such as supporting motor regulation by containing the infant with swaddling. The majority of research on interventions using this model have focused on the infant in the hospital environment, with reports of varying success[19,20]. Dolby et al[6] designed their study to incorporate the principles of self-regulation but hypothesized that a home-based program would be more beneficial as it could target the parents specifically.

### Attachment Theory

Attachment refers to the relationship and special emotional bond that infants develop with their caregivers over the first year of life[21]. Attachment is thought to develop over a period of time, as the adult and infant engage in interaction, and the infant organises his or her behavior around the care givers[21]. Attachment theory is based upon the biological need an infant has to interact with their environment[22]. From birth, infants can attend to the sound of a voice, and be soothed by human touch[23]. As mentioned previously, preterm infants may have altered self-regulation which can affect their ability to interact with their environment, and caregiver responsiveness is required. Positive early interactive experiences with a primary caregiver are believed to be an important process in "fine-tuning" the neural developmental systems and creating a secure infant. Attachment behavior and organization evolves in phases and is dependent on the age of the child[21]. During the first phase, from birth to three months, the caregiver learns to interpret and respond appropriately to the infant's fluctuating states and behavioral cues. The caregiver has an important role in setting limits of stimulation so the infant can remain organized. During the second phase, from three to six months, the infant becomes more communicative and responsive to their caregivers. The caregiver engages, relaxes, then re-engages with the infant in response to the infant's signals. Consequently, the infant can learn to maintain organized behavior with increasing levels of stimulation[22]. The infant may initiate engagement, but cannot maintain organization independently, and the caregiver thus has an important role in controlling their infant's state and behavior. During the next phase, from 6-12 months, the infant becomes more mobile and has an increased capacity for intentional behavior with the development of more motor control. A reciprocal attachment relationship develops when there has been a history of appropriate caregiver-orchestrated interactions during the first six months. The caregiver has an important role in providing a secure base for their infant so the infant can learn to be independent whilst being able to check that the caregiver is present, if needed [9].

Parents of infants born preterm may experience a range of responses following the birth, including depression [24-27], anxiety [28-30] and symptoms of post traumatic stress disorder[31]. Studies have also shown that parental stress is related to less sensitive, more intrusive and more active maternal interactional behavior[32]. There is some evidence that programs that are aimed at improving the parent-child interaction through providing emotional support in the way of information and education of infants' behavioral cues, encouragement and empathy increased parental feelings of self confidence and competence, and increased positive parent-infant interaction [33-35]. The study by Dolby et al[6] used the three phases of attachment development described by Sroufe above [22] to guide their intervention program.

Whilst the program by Dolby et al[6] has a strong theoretical background, the methodology (study design and subject numbers) and reporting of the results limits the conclusions that can be drawn from the study. Therefore, we conducted a randomized controlled trial, partly based upon the theoretical content of the Dolby et al[6] study, with the aim of improving the infant's motor and cognitive performance, the parent-infant relationship, and primary caregiver mental health outcomes. The original intervention model reported by Dolby et al[6] which was created in the 1980s, has been updated in the present intervention to account for current theories of development and research on early intervention[3]. In addition, this intervention targets very preterm infants who have been identified as being at high risk for developmental impairment. The VIBeS Plus program was designed for infants born at younger gestational ages (all infants will be born at <30 weeks' gestational age whereas the mean gestational age of the Dolby study infants was 32 weeks), with a higher incidence of multiple births, and with the study commencing later, at 40 weeks' gestation rather than before 40 weeks in the NICU. We have published a Cochrane review of early developmental interventions that demonstrated that interventions commencing post hospital discharge had similar effects on cognitive and motor development compared with interventions that commenced in the NICU[3]. The theoretical framework for the VIBeS Plus program incorporates the theoretical models used in the study by Dolby et al[6] with the inclusion of dynamic systems theory and family centered practice model.

### Dynamic Systems Theory

Dynamic systems theory is a conceptual framework that evaluates motor behavior as emerging from the dynamic cooperation of many subsystems in a task specific context[7]. Dynamic systems are any system that changes over time, including not only the infant's central nervous system but also the biomechanical, psychological and social environments. This contrasts with the traditional beliefs about motor development, whereby the infant's motor performance is dependent on the interactions between the infant's inherent and emerging skills with that of the environment in which the task is being performed and the characteristics of the desired task[36].

Development is considered to be non-linear within this model, such that the infant may have times of rapid development and times where the infant is refining their skills. Infants will experience 'transition phases' associated with the infant learning a higher level skill[7]. During this time the infant's movement becomes highly variable as the infant experiments with different movement patterns. As the infant learns the most efficient way of moving, the skill will be refined. This model is consistent with Als' synactive model of neonatal behavioral organization[12] and Brazelton's theory of touchpoints[9]. Integration of new motor strategies occurs through a process of neuronal selection, in which neuronal connections associated with the most efficient movement patterns are strengthened through repeated use[37]. By creating an enriching environment, the infant should be motivated to move to interact with their surrounds. Our intervention is timed at stages of transition so the therapist has the ability to view how the infant learns and adapts to new tasks[38].

### (a) Family-centered care

The intervention program involves "family-centered care", where the health professional recognises the important role that families play in ensuring the health and well-being of children[39]. Intervention programs have typically been child-centered, with therapists being viewed as the "expert" and setting goals that focus on bringing about changes in the child[8]. However, this form of intervention is being challenged by family-centered practice which views the parent as knowing their child best, being a valuable resource and having tremendous insight into their child's abilities. Parents are increasingly involved in implementing home programs not only because of resource limitations within the healthcare system, but also because of the importance of family-centered care[40]. The principles of family-centered care are that the health professional recognises each child and their family's innate strengths, with the health care experience being viewed as an opportunity to build on strengths, and to support families in the care-giving and decision making roles. It identifies that each family is different and that the children function optimally within a supportive family and community context[8]. Family involvement is a key to intervention, as it means that activities can be incorporated into daily life and the infant can learn through repeated reinforcement of an activity. For example, if the therapist and family are working together on encouraging flexed, contained postures to help the infant settle, the family can hold the infant in flexion during feeding, nappy changes, play etc. The relationship between family and professionals is a partnership in which the families define the priorities for therapeutic intervention, with the therapist helping to direct the intervention process.

### VIBeS PLUS

The VIBeS Plus program is home-based with the infant's primary caregiver a central component in the intervention. Intervention commences early in the developmental process, at term, so that various subsystems that influence development from the musculo-skeletal system to the parent-infant relationship can be enhanced within weeks of the baby being discharged home. At each stage components of the intervention will take account of the infant's development, caregiver-infant interaction and the environment. The program employs a problem-based learning approach where the caregiver's concerns are addressed and strategies devised together with the therapist, rather than the didactic approach where an expert delivers therapy or teaches the mother.

## Methods/Design

The aim of this randomized controlled trial is to compare the VIBeS program, which is delivered over nine sessions by a team of a physiotherapist and psychologist, with routine post-discharge care. The outcomes for this trial are the infant's cognitive, motor, and language development, and behavioral regulation, as well as caregiver-child interaction and caregiver mental health at 24 months of age, corrected for prematurity. The study has been approved by the Royal Women's Hospital and Royal Children's Hospital Research and Ethics Committees.

### Study sample

Infants born at <30 weeks' gestational age with no major congenital anomalies associated with a poor neurodevelopmental outcome will be eligible for inclusion in this study. As the study involves home-based assessment and intervention, families will be required to live within a 100 km radius of the hospital. Families will need to speak English, as funding is not available for interpreters. Infants will be excluded if they are still in hospital at 4 weeks' corrected age, as the study is designed to target the primary care giver and infant in a home-based setting. Infants will be recruited from the Royal Women's Hospital or the Royal Children's Hospital, Melbourne, Australia. These hospitals represent two of the four neonatal intensive care units in the state of Victoria, Australia.

### Sample Size Calculations

The primary basis for sample size calculation is the comparison between treatment and control groups on cognitive and motor outcomes at 24 months of corrected age. We consider an important clinical difference to detect would be an improvement of at least 0.4 SD (6 points) in the cognitive and/or the motor scales of the Bayley Scales of Infant and Toddler Development - 3^rd ^edition[41]. With a type-I (alpha) level of 0.05, and 80% power, we will require 100 subjects in each group, i.e., a sample size of 200.

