### Randomization Process

Infants will be randomly allocated to the intervention and control groups by a computer-generated random sequence, with the treatment allocation concealed in opaque envelopes; only the trial statistician will have access to the code. As parents have the choice to participate in the study without their infant undergoing brain MRI, there will be three strata: 1) nil to mild white matter abnormality, 2) moderate to severe white matter abnormality, or 3) no-MRI group. Secondly, as infants of multiple births need to be randomized to the same group due the family being involved in the intervention, there will also be stratification for multiple births.

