### Analysis plan

Analysis will follow standard principles for randomized controlled trials, using simple two-group comparisons performed using all subjects for whom outcome data are available, on an intention-to-treat basis. The primary comparison at 24 months will be based on the Bayley cognitive and motor composite scores, which will be compared between groups using linear regression, controlling for multiple births. Multivariate regression will be used to adjust for potential imbalances in major baseline confounders such as the extent of brain injury (and sociodemographic variables). Secondary analyses will use similar methods to compare the outcomes between groups for the additional motor (NSMDA, AIMs); behavioral (ITSEA), primary caregiver mental health and parent -child interactions measures (VIBES, EAS) at 24 months. For dichotomous outcomes, comparisons will be by chi-squared tests and where continuous data exhibit substantial skewness, non-parametric (Mann-Whitney U test) methods will be used for simple comparisons, and regression analyses performed after appropriate transformation of the outcome.

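### The 200 infants are the bare requirement for independent observations, but siblings are randomized together, so the stated 80% power holds only if sibling correlation is trivial

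*Protocol article*

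**What the plan says.** The Sample Size Calculations section targets "an improvement of at least 0.4 SD (6 points) in the cognitive and/or the motor scales" at 24 months' corrected age, and concludes: "With a type-I (alpha) level of 0.05, and 80% power, we will require 100 subjects in each group, i.e., a sample size of 200". It mentions neither multiple births nor loss to follow-up, and it does not say whether the 200 are infants enrolled or infants assessed.

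The Randomization Process section states that "infants of multiple births need to be randomized to the same group due the family being involved in the intervention", and adds stratification for multiple births. The Background expects more multiple births than in the earlier trial on which the program is partly based, but gives no figure.

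The Analysis plan compares the Bayley cognitive and motor composites by linear regression that controls for multiple births. Comparisons are "performed using all subjects for whom outcome data are available, on an intention-to-treat basis".

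**The concern.** The randomization and analysis sections both recognise that multiples need special handling; the sample size section does not. Co-twins share a family, a home and, in the intervention arm, the same visits, so their Bayley scores are likely to be positively correlated. When both go to the same arm, the second twin adds less information about the treatment difference than an unrelated infant would. A sample size that counts every infant as independent then overstates the power.

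The Background justifies the trial partly by the scarcity of adequately powered trials of this kind, so readers will give weight to the power figure. As written, it describes a trial of 200 unrelated infants, all assessed, and not the one in the Randomization Process section.

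**Working it through.** **Inputs from the protocol.** Difference 6 points = 0.4 SD, so SD = 6/0.4 = 15. Alpha 0.05; sidedness is not stated, but two-sided reproduces the figure, whereas one-sided would need only 78 per group. Power 80%. 100 per group.

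**Inputs assumed, because the protocol gives none.** Share of infants in twin pairs, f = 20-40%. Sibling correlation, ICC = 0.4-0.8. Loss by 24 months: none, then 10%.

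**Step 1: reproduce the plan's figure.** n per group = 2(1.96 + 0.8416)²/0.4² = 98.1. With the t distribution the solution is 99.08, so 100 per group. Noncentral-t power is 79.97% at 99 per group and 80.4% at 100. The stated figure is reproduced with no adjustment, and the spare margin is 100/99.08 = 1.009. A design effect above about 1.009, or loss above about 1%, takes power below 80%. With f = 20% under ordinary regression, that design effect is reached at an ICC of about 0.009/0.2 = 0.05.

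**Step 2: effect of co-randomized twins.** Two versions are shown because the Analysis plan does not fix the estimator.

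- Ordinary regression with clustered variance: design effect = 1 + f × ICC.
- Efficient weighting (a mixed model, for example): information per infant = (1 − f) + f/(1 + ICC), and the design effect is its reciprocal.

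Effective n per group = 100 / design effect. Power is from the noncentral t. Detectable difference = 15 × 2.80 × √(2/effective n).

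| f, ICC | Method | Design effect | Effective n | Power, no loss | Detectable at 80% |
|---|---|---|---|---|---|
| 20%, 0.4 | Ordinary | 1.08 | 92.6 | 77.3% | 6.2 points |
| 20%, 0.4 | Efficient | 1.06 | 94.3 | 78.0% | 6.1 points |
| 30%, 0.6 | Ordinary | 1.18 | 84.7 | 73.5% | 6.5 points |
| 30%, 0.6 | Efficient | 1.13 | 88.8 | 75.5% | 6.3 points |
| 40%, 0.8 | Ordinary | 1.32 | 75.8 | 68.7% | 6.8 points |
| 40%, 0.8 | Efficient | 1.22 | 82.2 | 72.2% | 6.6 points |

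**Step 3: loss, only if 200 means infants enrolled.** With 10% loss, 90 per group remain, and power without clustering is 76%. Dividing 90 by the same design effects gives, for the three settings in order, 73%, 69% and 64% (ordinary) and 74%, 71% and 68% (efficient).

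**The case against.** - **The arithmetic is correct.** This stands. The figure reproduces; the difficulty is that its independence assumption conflicts with the randomization section. A reader might infer a calculation error, and there is none.
- **Loss may be covered elsewhere.** This largely stands. A condensed article may leave a retention assumption to the full protocol, and "we will require 100 subjects in each group, i.e., a sample size of 200" can mean enrolled or analysable infants. A reader might infer that the trial makes no allowance for loss; the article does not establish that. It leaves open what the 200 counts. The clustering point holds on either reading.
- **The size of the shortfall is assumed.** This stands. At 20% multiples and a correlation of 0.3, clustering alone leaves about 78%, which is a small deficit. A reader might infer that the true power is 65-75%. The documents do not support that: values below about 69% need assumed loss as well, and the ordinary-regression design effect is the less favourable of two that the Analysis plan allows.
- **Multiple births are stratified for and controlled for.** This does not answer the point. Neither step restores the information lost when co-twins share an arm.
- **Covariate adjustment regains precision.** In part. At a design effect of 1.18, baseline covariates explaining about 15% of outcome variance would bring power back to 80% without loss; about 23% would be needed with 10% loss. But the sample size takes no credit for adjustment, no explained variance is given, and the Analysis plan presents adjustment as a response to baseline imbalance.
- **Power matters little once results are in.** Fair. Whether a null result excludes 6 points is judged from the confidence interval, and neither bias nor type I error follows from the power figure.

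**Conclusion.** The point holds for clustering. That 200 infants give less than 80% power for 6 points follows from the protocol's own sections, given any more than trivial positive sibling correlation. The size does not follow from them. Under the assumed 20-40% of infants in twin pairs and correlation of 0.4-0.8, without loss, power is about 69-77% with ordinary regression or 72-78% with efficient weighting, and the detectable difference is about 6.1-6.8 points. Loss is conditional: if 200 is the number enrolled, an assumed 10% loss alone gives 76%, and combined with clustering about 74% down to 64% across both methods. The stated figure needs restating; the design does not need to change.

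**What to change.** Keep n=200 and revise the Sample Size Calculations section to:

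1. state the assumed share of infants from multiple births and the assumed sibling correlation;
2. say whether 200 means infants enrolled or infants assessed at 24 months, with the assumed loss if enrolled;
3. give the resulting power for 6 points, or the difference detectable at 80% power. As an illustration, 30% of infants in twin pairs with a correlation of 0.6 and no loss gives about 74-76% power, or about 6.3-6.5 points.

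Any precision expected from covariate adjustment can be shown alongside, with the assumed explained variance. The only cost is a less favourable stated figure: no extra infants, and no change to conduct or analysis.
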